## Abstract

**Background:**

Tobacco quitlines provide effective resources (eg, nicotine replacement therapy, smoking cessation counseling, and text and web-based support) for those who want to quit smoking in the United States. However, quitlines reach approximately only 1%-3% of people who smoke each year. Novel, smartphone-based, and low-burden interventions that offer 24/7 access to smoking cessation resources that are tailored to current readiness to quit may increase appeal, reach, and effectiveness of smoking cessation interventions.

**Objective:**

This study will examine the efficacy of OKquit, a low-burden smartphone-based app for smoking cessation.

**Methods:**

Approximately 500 people who smoke cigarettes and access the Oklahoma Tobacco Helpline (OTH) will be randomized to receive standard OTH care (SC) or SC plus the novel OKquit smartphone app for smoking cessation (OKquit). All participants will use a smartphone app to complete study surveys (ie, baseline, 27 weekly surveys, brief daily check-ins, and 27-week follow-up). Upon completion of daily check-ins and weekly surveys, participants will receive either trivia type messages (SC) or messages that are tailored to current readiness to quit smoking and currently experienced lapse triggers (OKquit). In addition, those assigned to receive the OKquit app will have access to on-demand smoking cessation content (eg, quit tips, smoking cessation medication tips). It is hypothesized that participants assigned to OKquit will be more likely to achieve biochemically verified 7-day point prevalence abstinence than those assigned to SC at 27 weeks post enrollment. In addition, participants who use more OTH resources (eg, more cessation coaching sessions completed) or more OKquit resources (eg, access more quit tips) will have greater biochemically verified smoking cessation rates.

**Results:**

Data collection began in September 2022 and final follow-ups are expected to be completed by May 2025.

**Conclusions:**

Data from this randomized controlled trial will determine whether the OKquit smartphone app combined with OTH care will increase smoking cessation rates over standard OTH care alone. If successful, OKquit could provide tailored intervention content at a fraction of the cost of traditional interventions. Furthermore, this type of low-burden intervention may offer a way to reach underserved populations of adults who smoke and want to quit.

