It has been suggested that smoking cessation interventions should focus on particular difficulties that smokers are likely to encounter as they transition from being not ready to quit in the next 30 days to maintaining a successful quit attempt (eg, see Transtheoretical Model [13-15]). The Transtheoretical Model has stimulated a tremendous amount of addiction research; however, some limitations have constrained its use [16]. More recently, the Phase-Based Model (PBM) of cessation treatment has been proposed which includes four cessation phases: (1) motivation, (2) precessation, (3) cessation, and (4) maintenance [17]. The PBM suggests that specific challenges and opportunities present themselves in each phase of a quit attempt and treatments should be “phase tuned” to address these challenges and opportunities.

Smartphone-based ecological momentary assessments (EMA) are used to capture an individual’s behaviors and experiences in their natural environments [18]. EMA data have been used to tailor health behavior change interventions to an individual’s needs in real time [19-22]. For example, EMA data have been used to develop a smoking lapse risk estimator that identified 80% of all smoking lapses within 4 hours of the first lapse [23]. The Smart-Treatment (Smart-T) app offered on-demand features and used this lapse risk estimator to tailor smoking cessation messages to the current needs of socioeconomically disadvantaged adults in real time [19,20]. Research has indicated that urges to smoke, stress, and easy access to cigarettes were significantly reduced after tailored messages were delivered via the Smart-T app [24].

This randomized controlled trial aims to examine the impact of an adjunctive smartphone-based smoking cessation intervention (OKquit) combined with standard care (SC) by the OTH versus OTH care alone on biochemically verified smoking abstinence 27 weeks after study enrollment. This randomized controlled trial will also examine the impacts of OTH service engagement and use of OKquit intervention content on smoking abstinence and key lapse risk factors. To our knowledge, no study has examined whether low-burden app-based adjunctive interventions can improve state-based smoking cessation quitline quit rates.

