During the randomization call, research staff review the “App Instructions” button, which explains all app features (see Figure 2), walk participants through the schedule of daily check-ins and weekly surveys, and explain that participants will receive a US $5 for completing each weekly survey. The US $5 weekly survey is available on Saturdays via a button in the app and via app prompts. When participants do not complete the weekly survey, research staff contact them via text, call, or email to check in and remind them of the importance of completing the daily check-ins and weekly surveys. The day after randomization, the app begins to prompt a brief daily check-in 30 minutes after waking, and participants select up to 5 additional brief check-ins they would like to receive for that day. All participants are prompted to complete the daily check-ins for the entire 27-week study duration.

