### Standard OTH Care (SC) Condition

Standard OTH services, including NRT (eg, nicotine patches, gum, and lozenges), phone-based counseling, and web-based intervention services are available to all participants. SC participants are prompted to complete brief daily check-ins and weekly surveys through the Insight app. In addition, SC participants have access to an on-demand one-click “Call Oklahoma Helpline” feature in their app. SC participants are able to advance through the 4 PBM phases (ie, Motivation, Pre–Quit, Post–Quit, and Maintenance); however, they do not receive tailored messages after each weekly survey or daily check-in. Instead, SC participants receive “factoid” or trivia-type messages at the completion of each check-in or weekly survey. These factoid messages serve as an attention control (see Table 1).

**Table 1 table1:** Message types and examples.

Message level	Phase/group	Example
1	Motivation (OKquit)	First name, after quitting smoking, ex-smokers report lower levels of stress than when they were smokers.
2	Pre-Quit (OKquit)	First name, after you quit smoking, you will be tempted to lapse. Reduce temptation by removing ashtrays, lighters, matches, and cigarette butts. These items can trigger cravings and reduce motivation for staying quit.
3	Post-Quit: Low Risk for Imminent Lapse (OKquit)	First name, sometimes people save a pack of cigarettes (or even a few cigarettes) “just in case” or to prove they have the willpower to not smoke. DON’T! This just makes it easier to start smoking again!
4a: Stress	Post-Quit/Maintenance: High Risk for Imminent Lapse (OKquit)	First name, right now, it may feel like smoking would be enjoyable. However, you will feel worse later on if you do smoke now. You can get through this time without smoking.
4b: Urge	Post-Quit/Maintenance: High Risk for Imminent Lapse (OKquit)	First name, when you crave a cigarette, focus on a happy memory and get away from it all for a moment. Concentrate on that memory and nothing else.
4c: Cigarette Availability	Post-Quit/Maintenance: High Risk for Imminent Lapse (OKquit)	First name, you may be tempted to smoke when you see someone smoking or smell smoke. Do something to keep your mind off smoking. Listen to music, read, call a supportive friend, or take a walk.
4d: Cessation Motivation	Post-Quit/Maintenance: High Risk for Imminent Lapse (OKquit)	First name, you are setting a great example for children and others in your life! Congratulations on quitting smoking!

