## Discussion

### Principal Results

This study will determine whether the OKquit app improves biochemically confirmed smoking cessation rates for OTH service users 27 weeks after enrollment. This study will also examine the effects of engagement with OTH services and OKquit intervention content on smoking abstinence and key lapse risk factors. To our knowledge, this will be the first study to examine the effects of a low-burden app-based adjunctive intervention on smoking cessation quitline quit rates.

Quitline services are evidence-based [1,8]; however, only 1%-3% of people who smoke register for quitline services each year [12,49]. Early versions of quitline services included phone counseling supplemented with mailed cessation materials. Over time, as technology has advanced, quitlines have expanded their offerings to include NRT (eg, nicotine patches, nicotine gum), web-based counseling, and mobile communications via text and email [9,10,50,51]. Adjunctive smartphone-based cessation apps such as OKquit could increase convenience, appeal, reach, and effectiveness of quitline services. Given that nearly all people in the United States own a smartphone [52], low-burden smartphone-based interventions may offer a novel way to administer empirically validated smoking cessation interventions. If using the OKquit app with and without use of standard helpline services increases biochemically verified smoking abstinence, then this type of intervention could help in the fight against smoking for individuals who might not otherwise have the means to take part in intensive smoking cessation programs. OKquit’s low-burden design includes brief daily check-ins that prompt thinking about cessation and provide useful cessation advice on how to cope with currently experienced lapse triggers. Furthermore, OKquit enables participants to access smoking cessation materials on demand and reinitiation of cessation attempts after lapse or relapse.

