### Limitations

Study participants are required to use their personal Android smartphone. Individuals whose Android phone does not meet app requirements, those unwilling to install the app on their personal smartphones, those without a smartphone, and iPhone users are unable to participate. Future interventions will use a new version of the Insight platform that works with all phone types. Another limitation is that the sample will focus solely on OTH users. Finally, this study will not examine the efficacy of OKquit as a stand-alone intervention for quitline users.

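### The stated comparator, OTH care alone, is received by no arm: the SC arm also uses the study app for 27 weeks, so the trial estimates only what OKquit's added content contributes

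*Protocol article*

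**What the plan says.** The abstract (Conclusions) says the data will determine "whether the OKquit smartphone app combined with OTH care will increase smoking cessation rates over standard OTH care alone". The last paragraph of the Introduction gives the aim as the impact of OKquit "combined with standard care (SC) by the OTH versus OTH care alone".

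The arms are described differently elsewhere. The abstract (Methods) says "All participants will use a smartphone app to complete study surveys". The section on the Standard OTH Care (SC) Condition says "SC participants are prompted to complete brief daily check-ins and weekly surveys through the Insight app", and describes the trivia messages as an attention control. Procedure adds: "All participants are prompted to complete the daily check-ins for the entire 27-week study duration". The OKquit Condition section gives OKquit participants everything the SC arm has, plus further features.

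Two later statements also bear on the claim. In the Discussion (Principal Results) an implication is drawn under the condition "If using the OKquit app with and without use of standard helpline services increases biochemically verified smoking abstinence". The Limitations say "this study will not examine the efficacy of OKquit as a stand-alone intervention for quitline users". They do not mention that there is no arm with helpline care only.

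**The concern.** The aim and the headline conclusion name a contrast (app plus helpline against helpline) that differs from the one randomized (enriched app plus helpline against basic app plus helpline). The protocol does not treat the shared part as inert. Compensation counts the daily check-ins among the treatment components. The Discussion credits OKquit with check-ins that make people think about quitting and with restarting quit attempts after a lapse, yet both arms have check-ins and can reset the quit date.

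At stake is how the result will be read. A null result reported against the stated aim would suggest that the app adds nothing to quitline care, although part of the app was in both arms. A positive result would be quoted as the gain over ordinary quitline service, which the trial does not measure.

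**Working it through.** **Step 1. What each arm receives.**

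| Component | SC | OKquit | Where stated |
|---|---|---|---|
| Standard OTH services | yes | yes | SC Condition |
| Quit date chosen in the app; can be reset at any time | yes | yes | Procedure |
| Morning check-in: cigarettes yesterday, current triggers, likelihood of smoking | yes | yes | Check-Ins |
| Up to 5 further check-ins a day, chosen by the participant | yes | yes | Procedure; Check-Ins |
| Weekly survey, paid US $5, with staff contact if missed | yes | yes | Procedure; Compensation |
| Slip assessments; movement through four phases | yes | yes | Procedure; SC Condition; Measures |
| One-click helpline call | yes | yes | Procedure; SC Condition |
| Message after each check-in or survey | trivia | tailored | SC Condition; Automated Messages |
| Quit tips, medication tips, additional resources | no | yes | On-Demand Content |
| Reminder of smoke-free days and money saved | no | yes | Check-Ins |

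Only the last three rows differ by arm, apart from a slightly different check-in introduction. No column is OTH services alone.

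**Step 2. What can be estimated.** Let A be the abstinence rate under OTH care alone, B under OTH care plus the shared app (the SC arm), and C under OTH care plus the full OKquit app. Then

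C − A = (C − B) + (B − A).

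The abstract and Introduction claim C − A. The trial estimates C − B. Nothing in the trial estimates B − A.

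- With the planning rates in Statistical Analysis, C − B = 18% − 9% = 9 points, so C − A = 9 points + (B − A), with the second term unknown.
- If C − B = 0, then C − A = B − A, which is still unknown. A null result says nothing about the whole app against OTH alone.
- If B − A ≥ 0, then C − A ≥ C − B. A significant positive C − B then supports C > A in direction, but not in size.

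**Step 3. Whether the sample size calculation is affected.** Inputs from Statistical Analysis: 250 per arm, alpha .05 (taken as two-sided), Pearson chi-square, 18% against 9%.

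Power = Φ{ [d − 1.96·√(2p̄(1 − p̄)/n)] / √([p₁(1 − p₁) + p₂(1 − p₂)]/n) }

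With d = 0.09 and p̄ = 0.135: null SE = √(0.23355/250) = 0.03057; alternative SE = √(0.2295/250) = 0.03030; power = Φ[(0.09 − 0.0599)/0.0303] = Φ(0.993) = 0.840. The protocol's 84% reproduces.

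The documents give no effect for the shared app, so the following lifts in the SC rate are assumptions for illustration:

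| SC rate | Power, OKquit held at 18% | Power, both arms lifted equally (difference 9 points) |
|---|---|---|
| 9% | 84% | 84% |
| 10% | 73% | 82% |
| 11% | 60% | 80% |
| 12% | 47% | 78% |

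OKquit participants have the same shared features, so the right-hand column is at least as natural as the middle one. Neither shows an error in the plan, and the point does not depend on them.

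**The case against.** An attention-control comparator is a legitimate design, and it is disclosed: the abstract's Methods say that everyone uses the app and that SC receives trivia, before the conclusion is stated. Standard OTH care (SC) is also a defined arm label. All of this stands. It makes the design sound, but it does not make the word alone correct in the aim and the conclusion.

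Several stronger readings are tempting, and the documents do not support them:

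- *That the trial can say nothing about OTH care alone.* Too strong. If the shared content does not lower quit rates, the comparison is conservative and the direction carries over.
- *That the hypothesis is misstated.* It is not. The abstract and Statistical Analysis compare OKquit with participants assigned to SC, which is the randomized contrast.
- *That SC participants report smoking and triggers six times a day.* The text lists those items for the morning check-in. The cigarette count concerns the previous day, and the extra check-ins are optional with their items not listed.
- *That the Discussion plans an analysis of OKquit without helpline services.* The sentence is conditional and no such analysis is planned. It is one phrase at odds with the Limitations.
- *That the trial is underpowered because the SC app raises the control rate.* Only the case with OKquit fixed at 18% gives a large loss. The 9% is assigned to the SC intervention on the strength of earlier work that is not at hand, so it cannot be said whether that work involved similar app monitoring.

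**Conclusion.** The concern holds as a mislabelled comparator and an over-broad conclusion. It is not an invalid comparison or a wrong calculation. The trial estimates the effect of OKquit's tailored messages and on-demand content over OTH care plus an attention-control assessment app. It does not estimate the size of the whole app's effect over OTH care alone, and a null result would not rule such an effect out. Superiority over OTH alone could be inferred in direction only, on the untested assumption that the shared content does not lower quit rates. The gap, B − A above, has no figure in the documents and cannot be sized.

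**What to change.** 1. In the abstract's conclusion and the Introduction's aim, name the comparator as OTH care plus app-based check-ins with attention-control messages.
2. Limit the conclusion to the effect of OKquit's added content, and say that the effect of the whole app over OTH care alone is not estimated.
3. Add the absence of an OTH-only arm to the Limitations.
4. In Principal Results, delete the phrase about use with and without helpline services, so that it agrees with the Limitations.

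The hypothesis, endpoint, analysis and sample size need no change. If power scenarios for a higher SC rate are shown at all, include the equal-lift case (82%, 80%, 78%) beside the other. The cost is wording only; the downside is a narrower claim.

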**Trial Registration:**

ClinicalTrials.gov NCT05539209; https://clinicaltrials.gov/study/NCT05539209

**International Registered Report Identifier (IRRID):**

DERR1-10.2196/56827

## Introduction

Cigarette smoking continues to be the leading cause of preventable disease and death in the United States [1]. Recent estimates indicate that approximately 11.5% of adults in the United States smoke cigarettes [2]. According to the Centers for Disease Control and Prevention, smoking-related mortality accounts for as many as 480,000 deaths annually in the United States [3]. In 2004, the National Cancer Institute and the Centers for Disease Control and Prevention collaborated to establish a national telephonic portal for tobacco cessation quitlines using a toll-free number, [name]. This portal works by connecting callers directly with their appropriate state quitline. The effectiveness of tobacco quitlines has been well established in the literature [4-7]. In fact, both the 2008 US Public Health Service Clinical Practice Guideline and the 2020 Smoking Cessation Report of the Surgeon General endorsed state quitlines as an evidence-based method for tobacco cessation [1,8].

The Oklahoma Tobacco Helpline (OTH) was launched in 2003 to provide telephone-based tobacco cessation services to Oklahomans who want to quit smoking. The helpline is primarily funded by the Oklahoma Tobacco Settlement Endowment Trust to offer free, statewide services. OTH offers a variety of cessation services including phone counseling, automated email and text-based support, and nicotine replacement therapy (NRT, ie, nicotine patches and lozenges or gum) [9]. Over the past 2 decades, more than 490,000 Oklahoma tobacco users have received services from the program [10]. The North American Quitline Consortium has repeatedly ranked OTH as a leader in state-supported tobacco quitlines. In fact, between 2019 and 2022, the OTH had the highest reach of any US state quitline [11]. Despite its impressive ranking compared with other quitlines, OTH reaches only 3.1% of all Oklahomans who smoke annually, which leaves a large majority of Oklahomans who smoke unreached by OTH services [12].

It has been suggested that smoking cessation interventions should focus on particular difficulties that smokers are likely to encounter as they transition from being not ready to quit in the next 30 days to maintaining a successful quit attempt (eg, see Transtheoretical Model [13-15]). The Transtheoretical Model has stimulated a tremendous amount of addiction research; however, some limitations have constrained its use [16]. More recently, the Phase-Based Model (PBM) of cessation treatment has been proposed which includes four cessation phases: (1) motivation, (2) precessation, (3) cessation, and (4) maintenance [17]. The PBM suggests that specific challenges and opportunities present themselves in each phase of a quit attempt and treatments should be “phase tuned” to address these challenges and opportunities.

Smartphone-based ecological momentary assessments (EMA) are used to capture an individual’s behaviors and experiences in their natural environments [18]. EMA data have been used to tailor health behavior change interventions to an individual’s needs in real time [19-22]. For example, EMA data have been used to develop a smoking lapse risk estimator that identified 80% of all smoking lapses within 4 hours of the first lapse [23]. The Smart-Treatment (Smart-T) app offered on-demand features and used this lapse risk estimator to tailor smoking cessation messages to the current needs of socioeconomically disadvantaged adults in real time [19,20]. Research has indicated that urges to smoke, stress, and easy access to cigarettes were significantly reduced after tailored messages were delivered via the Smart-T app [24].

This randomized controlled trial aims to examine the impact of an adjunctive smartphone-based smoking cessation intervention (OKquit) combined with standard care (SC) by the OTH versus OTH care alone on biochemically verified smoking abstinence 27 weeks after study enrollment. This randomized controlled trial will also examine the impacts of OTH service engagement and use of OKquit intervention content on smoking abstinence and key lapse risk factors. To our knowledge, no study has examined whether low-burden app-based adjunctive interventions can improve state-based smoking cessation quitline quit rates.

## Methods

### Ethical Considerations

The University of Oklahoma Health Sciences Center institutional review board approved the protocol presented in this paper (reference number 14792). This trial is registered at ClinicalTrials.gov (NCT05539209). All participants provide informed consent, are notified that they can earn up to US $225 for completing study measures, and that they can withdraw from the study at any time without consequence. Data sets are deidentified via a subject identification number.

